## Hypothesis

The main objective of this study is to strengthen the evidence for clinical efficacy of tDCS in patients with mild cognitive impairment, while simultaneously embedding a mechanistic neuroimaging and electrophysiological perspective, and comparing the clinical effectiveness to determine if repeated stimulation over the parietal memory network or the DLPFC will yield measurable differences in improvements in cognitive performances compared with sham stimulation. Our secondary hypotheses aim to evaluate whether these cognitive improvements will be mediated by modulation of network-level integrity in the PMN and DMN, as will be assessed through resting-state functional MRI (fMRI) and EEG connectivity measures.

Regarding the rTMS, there have been considerable recent studies that analyzed the efficacy and safety of rTMS and tDCS in individuals with cognitive impairment and patients with Alzheimer’s Disease and MCI, and even in healthy individuals. For instance, several rTMS studies (Hanoglu et al., 2022, 2023) are showing promising results in AD, MCI, and PD (Jung et al., 2024; Zhang et al., 2022). A recent meta-analysis of 22 studies (1,074 patients) provides a good example of the beneficial effect of rTMS in AD and MCI, confirming the results by Hou et al. (2024). Also, a very recent work by Jung et al. showed that hippocampus and precuneuss- targeted repetitive transcranial magnetic stimulation (rTMS) increased functional connectivity and improved cognitive test scores in early AD patients (Jung et al., 2024).

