## Evaluation of the hypothesis

As briefly mentioned above, the primary endpoint of this study is the effect of anodal tDCS on cognitive improvement in patients with MCI, as measured by changes in performance on a standardized neurocognitive test battery. Composite *z*-scores will be derived for parietal memory network–related memory measures (primary composite outcome) and executive-function tasks (key secondary cognitive outcomes). Cognitive assessments will be performed at baseline, immediately after the intervention (Day 14), and at follow-up (Day 90).

The secondary endpoints are the neural correlates of stimulation-induced cognitive changes, assessed through multimodal neuroimaging and electrophysiological measures. Resting-state functional MRI will be used to evaluate alterations in structural and functional connectivity within the default mode network (DMN), parietal memory network (PMN), and hippocampal regions, alongside entropy measures (Shannon and permutation entropy). Quantitative Electroencephalogram (EEG) will be used to capture changes in electrophysiological activity, including power spectral density, coherence, and network connectivity indices. These secondary measures will provide connection insights into the network-level effects of tDCS and their relationship to cognitive outcomes.

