### Statistical analyses

All statistical analyses will be conducted using IBM SPSS Statistics, version 29.0 (IBM Corp., Armonk, NY, United States).

Analyses will be performed stratified by diagnosis (AD-MCI and PD-MCI):

*Neurocognitive outcomes:* Within each diagnosis group, repeated-measures ANOVA/GLM will be used with Time (Baseline, Day 14, Day 90) as a within-subject factor, Group (Real vs. Sham) and Target (DLPFC vs. LPC) as between-subject factors, and age, sex, education, and baseline global cognition as covariates. Planned contrasts will test the Group × Target × Time interaction separately in AD-MCI and PD-MCI. Between-diagnosis comparisons will then examine whether the effect of stimulation differs between AD-MCI and PD-MCI by including Diagnosis (AD-MCI vs. PD-MCI) as an additional between-subject factor. Post-hoc tests will be adjusted with Bonferroni correction.

*fMRI outcomes:* Resting-state fMRI data will be analyzed separately within AD-MCI and PD-MCI groups to assess functional connectivity within DMN, PMN, and hippocampal regions, as well as entropy metrics (Shannon and permutation entropy). Longitudinal changes (Baseline, Day 14, Day 90) and group differences (Real vs. Sham; DLPFC vs. LPC) will be assessed using repeated-measures ANOVA/ANCOVA with the same covariates.

After stratified analyses, diagnosis will be included as a factor to test for Diagnosis × Group × Target × Time interactions.

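### The only contrast named for the primary cognitive endpoint tests whether the tDCS effect differs between sites; real versus sham is in the model but is not designated

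*Protocol article*

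**What the plan says.** All references are to the protocol article.

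- **Objective.** The Hypothesis section opens with "The main objective of this study is to strengthen the evidence for clinical efficacy of tDCS in patients with mild cognitive impairment". The same sentence goes on to compare the two stimulation sites and asks whether stimulating them "will yield measurable differences in improvements in cognitive performances compared with sham stimulation".
- **Endpoint.** Under Evaluation of the hypothesis, "the primary endpoint of this study is the effect of anodal tDCS on cognitive improvement in patients with MCI". The primary outcome is a memory composite z-score, and testing takes place at baseline, Day 14 and Day 90.
- **Model for cognition.** Statistical analyses specifies a repeated-measures ANOVA/GLM within each diagnosis, with Time within subject, "Group (Real vs. Sham) and Target (DLPFC vs. LPC) as between-subject factors", and four covariates.
- **Contrast for cognition.** One is named: "Planned contrasts will test the Group × Target × Time interaction separately in AD-MCI and PD-MCI".
- **Step across diagnoses.** Diagnosis is added as a factor to "examine whether the effect of stimulation differs between AD-MCI and PD-MCI".
- **Post-hoc tests.** "Post-hoc tests will be adjusted with Bonferroni correction". The comparisons are not listed.
- **fMRI, a secondary outcome.** Here the two-group comparisons are named: "group differences (Real vs. Sham; DLPFC vs. LPC) will be assessed using repeated-measures ANOVA/ANCOVA with the same covariates".

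**The concern.** The contrast singled out for the primary endpoint is an effect-modification contrast. It compares the real-minus-sham change at one site with that at the other. A treatment that works equally well at both sites gives an expected value of zero. A significant result would not show that either site beats sham, since it could arise from benefit at one site, harm at the other, or a mixture.

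The comparison that does address efficacy, real versus sham over time, is named for fMRI and not for cognition. With no efficacy contrast designated, Group × Time, the three-way term, the unnamed post-hoc tests and the four-way term could each later be presented as the result. A null on the named contrast could also be read as failure of a treatment that works.

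**Working it through.** **Inputs.** Cells per diagnosis are 20 real and 10 sham at each site (Figure 1 caption), so 40 real and 20 sham per diagnosis, and 80 and 40 overall. The effect size of 0.5 to 0.6, two-sided α of 0.05 and 20% dropout come from Power calculation. Assumptions made here: d is the standardised difference in change from baseline at a single visit (SD = 1), there is no covariate adjustment, and power is from the noncentral t.

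**The plan's own figure.** Power calculation gives 50 per group for 90% power. The usual formula, n per arm = 2(1.960 + 1.282)²/d², gives 85 at d = 0.5 and 59 at d = 0.6, so the figure does not reproduce for a two-arm comparison. That is a separate matter. It is noted because the sample size is tied to differences between stimulation conditions and not to a site interaction.

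**What each contrast estimates.** Let δD and δL be the real-minus-sham differences in change at DLPFC and LPC.
- Group × Target × Time estimates δD − δL.
- Group × Time estimates (δD + δL)/2.

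**Standard errors, one diagnosis.**
- Each site: variance 1/20 + 1/10 = 0.15.
- Three-way: √(2 × 0.15) = √0.30 = 0.548 SD.
- Real versus sham averaged over target: √(1/40 + 1/20) = √0.075 = 0.274 SD, half the three-way value.
- The same contrast over both diagnoses: √(1/80 + 1/40) = √0.0375 = 0.194 SD.

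**Power at d = 0.5 and d = 0.6.**

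| Contrast | Effect pattern | Full sample | After 20% dropout |
|---|---|---|---|
| Group × Target × Time, per diagnosis | equal at both sites | 5%, 5% | 5%, 5% |
| Group × Target × Time, per diagnosis | one site only | 15%, 19% | 13%, 16% |
| Real vs sham, per diagnosis | equal at both sites | 43%, 58% | 36%, 48% |
| Real vs sham, both diagnoses | equal at both sites | 73%, 87% | 63%, 78% |

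For example, at d = 0.6 at one site only, the three-way noncentrality is 0.6/0.548 = 1.10. For real versus sham with d = 0.6 at both sites it is 0.6/0.274 = 2.19.

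**Check by simulation.** 4,000 runs used three time points, correlation 0.5, cells of 20/10/20/10, and multivariate repeated-measures tests without covariates or dropout.
- d = 0.6 at both sites: Group × Time rejected in 59% of runs, the three-way term in 4.9%.
- d = 0.5 at both sites: 43% and 4.6%.
- d = 0.6 at one site only: 18% for each.

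The last line matters. When only one site works, averaging over target halves the effect (0.6 to 0.3), and 0.3/0.274 equals 0.6/0.548. The two contrasts then have the same power.

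**The case against.** The strongest reply is that real versus sham is already in the model. Group and Time are both factors, so a full-factorial fit also yields Group × Time. Adding Diagnosis yields the same term across diagnoses, even though the stated purpose of that step is effect modification. This stands. A reader might infer that the main objective has no planned test, or that the trial cannot answer its main question. The document does not support that: the test is available but not designated.

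A second reply is that the objective includes comparing the sites, so the three-way contrast is relevant. This also stands. The contrast answers part of the objective, with low power, but not the efficacy part.

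A reader might also infer that real versus sham is left to Bonferroni-adjusted tests of 20 against 10. The document lists neither the post-hoc comparisons nor their number, so neither that claim nor a power figure built on it measures the written plan. Nor is coding sham by target an error, because it mirrors randomisation to target first and to real or sham within target.

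Finally, a 5% rejection rate under equal effects is correct behaviour for an interaction test, and a fuller analysis plan may exist. Neither reply removes the point. The article does name its contrast for the primary outcome, and that contrast answers a different question from the endpoint.

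**Conclusion.** The point holds in this form: for the primary cognitive endpoint, the one planned contrast named tests effect modification by site, and the real-versus-sham contrast that matches the endpoint is not designated. The consequence is largest when tDCS works equally at both sites. The named contrast then rejects at 5%, against 43% to 58% per diagnosis for real versus sham and 73% to 87% over both diagnoses. If only one site works, the named contrast has about 15% to 19% power, and averaging over target does no better.

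The figures assume d of 0.5 to 0.6 at a single visit, full recruitment and no covariate adjustment. Adjustment for prognostic covariates would raise the non-null powers, but it cannot help a contrast whose expected value is zero.

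**What to change.** In Statistical analyses, neurocognitive outcomes:

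1. Name real minus sham in change from baseline on the primary memory composite, averaged over target (Group × Time), at one stated visit, as the primary planned contrast within each diagnosis.
2. Report the same contrast from the model that includes Diagnosis (80 versus 40).
3. Make Group × Target × Time a secondary site comparison, and the four-way interaction with Diagnosis exploratory.

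The cost is wording, best settled before unblinding, with no change to recruitment, allocation or treatment. The downside is that the site comparison loses its place as the named planned contrast. The change does not cure the limited per-diagnosis power either, and averaging over target dilutes an effect present at only one site.

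Pooling sham across sites for site-versus-sham contrasts is optional. It lowers the variance of each from 0.15 to 1/20 + 1/20 = 0.10, but assumes that the sham response does not depend on electrode site. Moving the primary analysis to all 120 patients is likewise not required, since the plan stratifies and sizes by diagnosis.

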### Power calculation

The sample size was informed by previous studies applying tDCS in populations with cognitive impairment. For example, Khedr et al. administered active and sham tDCS to the left DLPFC over 10 consecutive days in 34 participants (Khedr et al., 2014). Additionally, the same group has shown efficacy of tDCS with the anode (positive electrode) placed at the T3-P3 or T4-P4 in 46 AD patients (Khedr et al., 2019).

Based on these precedents, and assuming a medium effect size (Cohen’s d ≈ 0.5–0.6) as reported in prior MCI/AD and motor adaptation studies, we calculated that a minimum of 50 participants per group would be required to achieve 90% power (1–*β* = 0.9) at a two-tailed *α* = 0.05. To allow for an anticipated dropout rate of approximately 20%, we increased the target to 60 participants in each diagnostic group (AD-MCI and PD-MCI), yielding a total sample of 120 participants. This sample size ensures sufficient power to detect clinically meaningful differences in cognitive outcomes between stimulation conditions.

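### The only contrast planned for the cognitive outcomes compares the two stimulation sites; the real-versus-sham test that the efficacy objective needs is not designated

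*Protocol article*

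**What the plan says.** The Hypothesis section gives a compound main objective. One part is to strengthen the evidence that tDCS works. The other is to compare the parietal and DLPFC sites and find whether stimulation there "will yield measurable differences in improvements in cognitive performances compared with sham stimulation". The section Evaluation of the hypothesis states that "the primary endpoint of this study is the effect of anodal tDCS on cognitive improvement in patients with MCI", with a memory composite as the primary composite outcome; no site difference enters that definition. The Power calculation section closes with "This sample size ensures sufficient power to detect clinically meaningful differences in cognitive outcomes between stimulation conditions".

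For the neurocognitive outcomes, the Statistical analyses section fits, within each diagnosis, a repeated-measures model with Time (three visits) and "Group (Real vs. Sham) and Target (DLPFC vs. LPC) as between-subject factors", plus four covariates. It then says "Planned contrasts will test the Group × Target × Time interaction separately in AD-MCI and PD-MCI". The other named comparison is again an interaction: "Between-diagnosis comparisons will then examine whether the effect of stimulation differs between AD-MCI and PD-MCI". Anything further falls under "Post-hoc tests will be adjusted with Bonferroni correction", and those tests are not listed. The fMRI paragraph of the same section does list real versus sham and DLPFC versus LPC as group differences to be assessed. The cognitive paragraph, which carries the primary endpoint, has no such statement.

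**The concern.** The contrast singled out in advance asks whether the benefit over sham differs between the two sites. The efficacy objective, the primary endpoint and the power statement ask whether there is a benefit over sham. The two questions can have opposite answers. Equal benefit at both sites leaves the interaction at zero. Benefit at one site with harm at the other can make it large with no net benefit.

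What is at stake is pre-specification. The efficacy result would have to be picked out of the model output, or reported as one of an unstated number of corrected post-hoc tests, while the contrast with planned status answers only the site question and is the less precise of the two.

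**Working it through.** **Inputs.** Cell sizes come from the Abstract and the Figure 1 caption: target 1:1, then real to sham 2:1. Reading the caption's numbers as per stimulation arm, each diagnosis has 20 real and 10 sham at each target, so 40 real and 20 sham. Effect size d = 0.5 to 0.6 and two-sided α = 0.05 come from the Power calculation section. Assumptions, because the article gives no SD or within-subject correlation: outcome is one change score with SD 1, and covariates bring no gain in precision.

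**The plan's own figure.** The article states 50 per group "to achieve 90% power". A two-sample comparison with equal arms needs n = 2(1.960 + 1.282)²/d² per arm: 85 at d = 0.5, 70 at 0.55 and 59 at 0.6. Fifty per arm gives 70.5% to 85.1% power over that range. So 50 is not reproduced from the stated inputs. This is a separate matter, and nothing below depends on it.

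**What each contrast estimates.** Let e_D and e_L be the real-minus-sham differences in change at DLPFC and LPC.

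- Group × Time, averaged over targets: (e_D + e_L)/2
- Group × Target × Time: e_D − e_L

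If e_D = e_L = d, the first is d and the second is d − d = 0. This holds for any d, any SD and any choice of visit.

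**Standard errors, per diagnosis.** The sum of 1/n over the four cells is 1/20 + 1/10 + 1/20 + 1/10 = 0.30.

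- Group × Time: ½·√0.30 = 0.274 SD, the same as √(1/40 + 1/20)
- Group × Target × Time: √0.30 = 0.548 SD, twice as large and so four times the variance

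**Power** (noncentral t, 60 − 4 = 56 df, two-sided 0.05):

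| Scenario | Group × Target × Time | Group × Time, averaged over targets |
|---|---|---|
| Both sites, d = 0.5 | 5% | 43% |
| Both sites, d = 0.6 | 5% | 58% |
| One site only, d = 0.5 | 15% | 15% |
| One site only, d = 0.6 | 19% | 19% |

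In 20,000 simulated trials per effect size with equal effects at both sites, the interaction rejected in 4.9% and 5.0%, and Group × Time in 43.3% and 57.6%. With 50 completers per diagnosis, lost pro rata (an assumption), the equal-effect power of Group × Time falls to 37% and 50%, and the interaction stays at 5%.

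The last two rows agree because averaging halves both the effect (d/2) and the standard error. For 90% power the interaction needs a site difference of about (1.960 + 1.282) × 0.548 = 1.78 SD, roughly three times the upper assumed effect of 0.6.

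**Real versus sham within one target** (20 against 10). The standard error is √(1/20 + 1/10) = 0.387 SD. With the same 56 df, power at d = 0.5 to 0.6 is 16% to 23% at α = 0.025 (two targets). It is 11% to 16% at α = 0.0125 (an assumed four site-by-visit tests; the article does not say how many post-hoc tests there are).

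**The case against.** Four objections carry weight.

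- **The objective includes a site comparison.** The three-way contrast is the right test of that part, so it belongs in the plan. This stands, and it is why the contrast should be kept. It does not supply the test against sham.
- **Equal benefit is not what the authors predict.** The Hypothesis section expects DLPFC and LPC stimulation to help, but does not say equally. The Discussion cites healthy-subject data in which parietal stimulation did better than other sites. The 5% figure is therefore the limiting case. This stands; but with one site wholly inactive the contrast still has only 15% to 19% power.
- **Real versus sham is in the model.** A reader might infer that the plan cannot test efficacy, that a null interaction would be read as failure of tDCS, or that real versus sham will be tested only if the interaction is significant. The article supports none of these. Group × Time follows from the stated factors, and nothing calls the interaction primary, decisive or a gate.
- **An article condenses, and the analysis plan is not shown.** Leaving the primary contrast unnamed would be no finding by itself. Here, however, the article does name a planned contrast, and that contrast does not match the efficacy objective.

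The power figures also simplify: they use a single-df test on one change score, where the article has three visits and four covariates. Covariates or a different SD would move the percentages. They would not move the zero under equal effects, and a different SD leaves the two-to-one ratio of standard errors unchanged.

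**Conclusion.** The point holds as a mismatch of designation and should be fixed. The one contrast planned for cognition tests whether the effect differs by site, while the efficacy question has no designated test. If both sites have the assumed d of 0.5 to 0.6, the planned contrast rejects at its type I error rate of about 5%, where real versus sham on the same patients rejects about 43% to 58% of the time. The zero is algebraic. The percentages rest on 20/10/20/10 per diagnosis, change-score SD 1 and no covariate gain.

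It would go too far to say that the trial's conclusion is decided by the wrong test. The article states no such decision rule, and the efficacy test can be obtained from the model it specifies.

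**What to change.** In the neurocognitive paragraph of Statistical analyses, name real versus sham (Group × Time) on the memory composite as the planned primary contrast within each diagnosis. Keep Group × Target × Time as a secondary test of whether the effect differs by site.

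The sponsor has a choice to make and state: average over the two targets, or test each target with multiplicity control. Averaging is more precise when both sites work but dilutes the effect when only one does (15% to 19% power). Per-target tests fit a site-specific expectation but rest on 20 against 10 patients (16% to 23% at α = 0.025).

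The cost is one sentence, with the same model and data and no extra patients. The change aligns the planned test with the efficacy objective; it does not bring power to the 90% claimed in the Power calculation section, which needs separate attention.

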#### Neuroimaging

Before the first tDCS stimulation session, participants underwent resting-state functional MRI (fMRI) data acquisition, which was repeated immediately after the completion of the stimulation series, following the 90^th^ day.

fMRI will evaluate structural and functional connectivity, with a specific focus on the default mode network (DMN), parietal memory network (PMN), and hippocampal connectivity. Network entropy will be computed using both Shannon and permutation entropy approaches.

R4 In detail, the processing step of the structural and functional connectivity will follow using the FreeSurfer (2025) and CONN Toolbox (2025). EEG pre-processing and connectivity analyses will follow standardized pipelines using open-source software (e.g., EEGLAB). Given the previous literature indicating the role of underlying connectivity and electrophysiological features of non-impaired structural brain regions in early dementia, we will pay special attention to the connectivity analysis. This will be assessed both at the ROI-to-ROI level and through whole-brain network analyses using the CONN Toolbox, with a focus on the parietal memory network (PMN) and default mode network (DMN). Entropy measures will be derived from resting-state correlation matrices to capture network complexity and integration. The calculation for different types of entropies will be performed according to the previously defined codes by Rostaghi and Azami (2016), which have already been used in our previous study (Yulug et al., 2025). The correction for multiple comparisons, family-wise error correction, will be applied, while for ROI-based analyses, correction will be used across the predefined set of regions to minimize false positive values.

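### The fMRI analysis names no contrast that isolates stimulation-induced network change, and the scope of its multiplicity correction is left undefined

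*Protocol article*

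**What the plan says.** Under Evaluation of the hypothesis, the Protocol article defines the secondary goal: "The secondary endpoints are the neural correlates of stimulation-induced cognitive changes, assessed through multimodal neuroimaging and electrophysiological measures". The Hypothesis section adds that cognitive gains should be mediated by modulation of the parietal memory and default mode networks, and it fixes sham as the comparator.

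For fMRI, the Statistical analyses section covers "functional connectivity within DMN, PMN, and hippocampal regions, as well as entropy metrics (Shannon and permutation entropy"), separately in each diagnosis. The effects to be assessed are: "Longitudinal changes (Baseline, Day 14, Day 90) and group differences (Real vs. Sham; DLPFC vs. LPC) will be assessed using repeated-measures ANOVA/ANCOVA". The covariates are those of the cognitive model: age, sex, education and baseline global cognition. After the stratified analyses, "diagnosis will be included as a factor to test for Diagnosis × Group × Target × Time interactions".

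The cognitive paragraph just above is more specific: "Planned contrasts will test the Group × Target × Time interaction separately in AD-MCI and PD-MCI". It also says "Post-hoc tests will be adjusted with Bonferroni correction".

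The Neuroimaging section gives two statements on multiplicity for fMRI. One is general: "The correction for multiple comparisons, family-wise error correction, will be applied". The other is narrower: "for ROI-based analyses, correction will be used across the predefined set of regions to minimize false positive values".

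**The concern.** The question is whether real stimulation changes the networks more than sham does. That calls for a Real-minus-Sham difference in change, or in the post-treatment value given baseline. The fMRI paragraph names neither, and taken at face value each effect it lists answers something else:

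- **Change over time** pools real and sham patients, so any shift common to both arms (rescanning, disease course, scanner drift) counts towards it.
- **Real vs. Sham**, if taken as a difference averaged over visits, includes the pre-treatment scan. That dilutes the effect and carries in any chance baseline imbalance.
- **DLPFC vs. LPC** includes the one third of each site arm that receives sham.
- **The four-way interaction** is null whenever stimulation acts alike in both diagnoses or at both sites.

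With no deciding term named, several different results could be reported as network modulation. Nor does any stated correction say that it reaches across connectivity, the two entropy metrics or the two diagnoses. The trial's mechanistic conclusion rests on this analysis.

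**Working it through.** The article gives no power or sample size for fMRI, so there is no figure to reproduce. What follows is an illustration.

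**Inputs from the article.** Per diagnosis, 20 real and 10 sham at each of two sites (Figure 1 legend), hence 40 real vs. 20 sham. Two-sided 5% (Power calculation).

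**Assumptions.** Effect d = 0.6 after baseline, borrowed from the upper end of the 0.5–0.6 that the Power calculation assumes for cognition. Unit variance, equal correlation r between scans of 0.5 (range 0.3–0.7), no dropout. Neither d nor r is given for fMRI.

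**Scans.** The Figure 2 legend gives fMRI at baseline and follow-up only; the Statistical analyses section gives three time points; the Neuroimaging section can be read either way. Both cases are shown.

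**Power.** Noncentral t with 58 df and noncentrality (standardised effect) / √(1/40 + 1/20), where the denominator is 0.274. Numbers in the table are at r = 0.5, with the range for r = 0.3–0.7 in brackets.

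| Contrast | Standardised effect | At d = 0.6, r = 0.5 | Power (range) |
|---|---|---|---|
| Two scans, visit-averaged Real vs. Sham | (d/2)/√((1+r)/2) | 0.3/0.866 = 0.346 | 24% (22–27%) |
| Two scans, Group × Time | d/√(2−2r) | 0.6/1 = 0.600 | 58% (45–79%) |
| Two scans, follow-up adjusted for baseline | d/√(1−r²) | 0.6/0.866 = 0.693 | 70% (62–86%) |
| Three scans, visit-averaged Real vs. Sham | (2d/3)/√((1+2r)/3) | 0.4/0.816 = 0.490 | 42% (36–50%) |
| Three scans, Group × Time (mean post minus baseline) | d/√(1.5(1−r)) | 0.6/0.866 = 0.693 | 70% (56–90%) |
| Three scans, mean post adjusted for baseline | d/√((1+r)/2−r²) | 0.6/0.707 = 0.849 | 86% (82–95%) |

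**Time effect.** Suppose both arms shift by 0.3 SD and stimulation does nothing. With 60 patients, three scans and variance 1.5(1−r)/60, the Time contrast is significant 62%, 77% and 93% of the time at r = 0.3, 0.5 and 0.7 (normal approximation).

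**Site effect.** With two scans, a true difference between the real arms shows up in a visit-averaged DLPFC vs. LPC difference at 2/3 (share treated) × 1/2 (share of scans after treatment) = 1/3 of its size.

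**Multiplicity, if the correction covers regions only.** Three metrics (connectivity, Shannon entropy, permutation entropy) are each tested at 5% in two independent diagnoses:

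- Independent metrics: 1 − 0.95⁶ = 26%.
- Metrics correlated 0.5 or 0.8 within a patient (simulated): 23–24% and 19%.

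If both group factors are tested, Real vs. Sham and DLPFC vs. LPC are orthogonal, because the 2:1 ratio is the same at each site. That gives four independent sets of three correlated tests:

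- Independent metrics: 1 − 0.95¹² = 46%.
- Correlation 0.5: about 42%. Correlation 0.8: 34%.

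**The case against.** The strongest reply is that the model can already test the right thing. A repeated-measures ANOVA with Time within subjects and Group and Target between subjects contains Group × Time and Group × Target × Time. Adding diagnosis to reach a four-way term presupposes that the lower-order interactions are in the model. The text never calls the group differences overall or visit-averaged, and a condensed article may leave the deciding term to a fuller plan. A reader might infer that the analysis cannot detect a stimulation effect; the article does not support that. What stands is narrower. The authors chose to list effects for fMRI and left out the relevant one, although they named an interaction with Time for cognition. The ANCOVA wording does not cure this, because the carried-over covariates exclude the baseline fMRI value.

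A reader might also infer that multiplicity is controlled over regions and nowhere else. That is too strong: a general family-wise correction is stated as well. Its family is undefined, so the error rates above are conditional.

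Finally, the power figures borrow a cognitive effect size and assume a scan correlation. That is fair, and they show only how the contrasts rank and roughly how far apart they lie. A lower d reduces all of them: at d = 0.5 and r = 0.5 they are 17.9%, 43.5% and 54.5% with two scans, and 31.1%, 54.5% and 71.9% with three. The anticipated dropout of about 20% would reduce them further.

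**Conclusion.** The point holds as a moderate one on a secondary endpoint. The fMRI paragraph names no contrast for Real-minus-Sham change and does not use the baseline fMRI value as a covariate. Under the stated assumptions at d = 0.6 and r = 0.5, moving from Group × Time to a baseline-adjusted contrast raises power from 58% to 70% (two scans) or from 70% to 86% (three). A visit-averaged group difference would have 24% or 42%, but that figure applies only if the group differences are read that way.

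On multiplicity, the gap is an undefined family. If the correction stops at regions, the family-wise rate is about 19–26%, or 34–46% with both group factors. It would be wrong to conclude that a false-positive network finding is more likely than not: every one of these rates is below one half.

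**What to change.** In the fMRI paragraph of Statistical analyses:

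1. Name one deciding contrast: Real minus Sham in the post-treatment value of one pre-named fMRI measure, adjusted for that patient's baseline value of the same measure. Parietal memory network connectivity would be one candidate; the choice is the sponsor's. Naming Group × Time is an alternative with less power, not an equivalent.
2. Test site only as Group × Target on that same baseline-adjusted outcome.
3. Label the remaining fMRI results exploratory (other networks, entropy metrics, repeats by diagnosis, the four-way term), or define the correction family in Neuroimaging to include metrics and diagnoses, for example with Holm on top of the regional correction.
4. Reconcile the fMRI visits between the Figure 2 legend, Neuroimaging and Statistical analyses.

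The first three changes are wording only and need no added patients, scans or data; the fourth asks the sponsor to state which scans are planned. All are most credible if made before unblinding. The cost is that most fMRI results are then reported as exploratory or face a stricter threshold.
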